# Innovations in the Management of Musculoskeletal Pain With Alpha-Lipoic Acid (IMPALA Trial): Study protocol for a Double-Blind, Randomized, Placebo-Controlled Crossover Trial of Alpha-Lipoic Acid for the Treatment of Fibromyalgia Pain

**DOI:** 10.2196/resprot.7198

**Published:** 2017-03-28

**Keywords:** fibromyalgia, pain, alpha-lipoic acid, antioxidants

## Abstract

**Background:**

Fibromyalgia is a common disorder characterized by chronic widespread pain, sleep disturbance, fatigue, depression, and cognitive dysfunction, resulting in substantial disability. As current analgesics provide incomplete relief and disabling side effects that aggravate fatigue and cognitive dysfunction, there is a need for new pain treatments with better efficacy and tolerability. Alpha-lipoic acid (ALA) is an antioxidant proven effective in painful diabetic neuropathy with minimal side effects.

**Objective:**

We hypothesize that this agent will provide benefits in fibromyalgia because of several similarities with neuropathic pain and also because it does not cause sedation, fatigue, or mental-slowing. To test this, we have designed a clinical trial that will assess pain, side effects, and other outcomes in participants with fibromyalgia.

**Methods:**

Using a crossover design, 24 adults with fibromyalgia will be randomly allocated to 1 of the 2 sequences of ALA and placebo. Participants will take capsules containing ALA or placebo for 4 weeks followed by a 1-week washout followed by a second 4-week treatment and 1-week washout period. ALA (or matching placebo) capsules will be titrated to 1800 mg/day over each 4-week period. The primary outcome will be mean daily pain intensity (0-10) during week 4 of each period. Secondary outcomes, assessed during week 4 of each period, will include global improvement, adverse events, mood, and quality of life.

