### Randomization and Blinding

We will use a balanced Latin Square crossover design in which participants will be allocated to one of the two treatment sequences of ALA and placebo. At the beginning of the trial, an investigational pharmacist will use a computer-generated randomization process to prepare a concealed allocation schedule to randomly assign the treatment sequences, in appropriate block sizes, to a consecutive series of numbers. On enrollment, each participant will be assigned to the next consecutive number, and the corresponding series of study medications will be dispensed (eg, ALA followed by placebo or placebo followed by ALA). Study medications will be formulated in an identical fashion across treatment periods. Treatment codes for each study participant will be generated by an investigational pharmacist and will not be disclosed to study personnel or participants until completion of all participants in the trial. Study outcome measures will be evaluated and recorded by the research study nurse who will be blinded (as will the rest of the research team) to treatment group assignments until trial completion. As an assessment of blinding to treatment group, each participant and the study nurse will complete a blinding questionnaire at the end of each treatment period.

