### Sample Size

Statistical considerations underlying this sample size calculation are based on the null hypothesis that there is no difference in pain intensity between the study treatments and the alternative hypothesis that ALA is different from placebo. Systematic reviews of placebo-controlled chronic pain trials consistently reveal that statistically significant treatment-placebo group differences vary between 0.5 and 1.5 points depending on the magnitude of placebo response in any given trial [32]. Thus, on the basis of previous estimates of within-participant variation in fibromyalgia [33], we project that a sample size of 21 participants would provide an 80% chance of detecting (at an alpha level of .05) a mean treatment group difference of 1.5 points on a 0-10 numerical rating scale. In order to have a sample size divisible by 4, we have adjusted the sample size to 24 participants. Accounting for trial dropout rates from our previous trials and for a 2-period crossover design, we expect that the recruitment of 30 enrollees for each trial will yield the above number of completers.

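### The abstract gives 24 as the number randomised, but the Sample Size section makes 24 the completers expected from 30 randomised

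*Protocol article*

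**What the plan says.** In the protocol article, the Methods paragraph of the abstract states that "24 adults with fibromyalgia will be randomly allocated to 1 of the 2 sequences of ALA and placebo". There 24 is the number randomised.

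The Sample Size section builds up to a different total. It states that "a sample size of 21 participants would provide an 80% chance of detecting (at an alpha level of .05". The effect in view is 1.5 points on the pain rating. The rounding comes next: "In order to have a sample size divisible by 4, we have adjusted the sample size to 24 participants". The section goes on to allow for dropout: "we expect that the recruitment of 30 enrollees for each trial will yield the above number of completers". There 24 is the number of completers and 30 the number enrolled.

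The Randomization and Blinding section ties enrolment to allocation: "On enrollment, each participant will be assigned to the next consecutive number, and the corresponding series of study medications will be dispensed". The Statistical Analysis section bases the efficacy analyses on participants who complete both periods and brings the others in only through sensitivity analyses.

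**The concern.** The same number, 24, is the number randomised in one place and the number remaining after dropout in another. Both can be true only if nobody drops out, and the Sample Size section expressly allows for dropout.

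The number randomised sets the length of the allocation schedule, the drug supply and the point at which recruitment ends. Because the efficacy analysis rests on completers, it also determines how many people carry the power. Anyone who later compares the conduct of the trial with the abstract would take 30 randomised as over-enrolment and 24 randomised as the plan fulfilled. Judged by the Sample Size section, it is the second outcome that risks falling short.

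**Working it through.** **Inputs from the protocol article**
- Needed for 80% power: 21 (Sample Size).
- Difference to detect: 1.5 points; alpha 0.05 (Sample Size). I take the test as two-sided because the section sets out "the alternative hypothesis that ALA is different from placebo".
- Completer target 24, enrollees 30 (Sample Size).
- Number randomised in the abstract: 24.

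**Not given:** a dropout rate and a standard deviation. The variability is referred to a cited source only. Both are therefore inferred below.

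**Step 1. The plan's own chain.**
- Rounding: 21 / 4 = 5.25, raised to 6, and 6 × 4 = 24.
- Implied loss: 1 − 24/30 = 0.20.
- Inflation: 24 / (1 − 0.20) = 30.

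The chain 21 → 24 → 30 is consistent. Since the 20% comes from 30 and 24 themselves, this shows consistency only and does not verify the rate.

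**Step 2. Completers if 24 are randomised**, using 24 × (1 − d):

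| Dropout d | Expected completers |
|---|---|
| 5% | 22.8 |
| 10% | 21.6 |
| 12.5% | 21.0 |
| 15% | 20.4 |
| 20% (implied) | 19.2 |
| 25% | 18.0 |

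The break-even rate is 1 − 21/24 = 12.5%.

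**Step 3. The standard deviation implied by the plan.** The 21 cannot be checked without a standard deviation, so I take it as correct and solve for the SD of the within-participant difference. With the normal formula n = (SD × (1.960 + 0.842) / 1.5)², SD = 1.5 × √21 / 2.802 ≈ 2.45. With the noncentral t distribution, SD ≈ 2.33 (n − 1 or n − 2 degrees of freedom).

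**Step 4. Power at other numbers of completers**, each method using its own SD:

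| Completers | Normal | t, n − 1 df | t, n − 2 df |
|---|---|---|---|
| 19 | 76.0% | 75.5% | 75.4% |
| 21 | 80.0% | 80.0% | 80.0% |
| 24 | 85.0% | 85.4% | 85.5% |

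If 21 was itself rounded up from just over 20, the SD is slightly smaller (2.39 by the normal formula) and power at 19 is at most about 78%, still under 80%.

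**Step 5. Chance of reaching 21 completers.** With each participant completing independently with probability 0.80, the binomial chance of at least 21 completers is about 26% with 24 randomised and about 94% with 30.

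**The case against.** The strongest reply is that the operative section is clear. The Sample Size section gives 21, then 24, then 30 without contradiction, and neither it nor the Randomization and Blinding or Recruitment sections suggests stopping at 24. On that view the abstract simply reports the target sample loosely. This stands as the likeliest explanation. It does not remove the error, because the abstract says in plain terms that 24 will be allocated.

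A second reply is that enrolment may not always mean randomisation. The Cointerventions and Rescue Medication section speaks of enrolled participants being weaned off ALA in a pretrial washout, and Table 1 places screening and baseline before treatment. Some of the loss from 30 to 24 could then come before the first dose, and 20% would overstate the loss after allocation. This makes the figure of 19 less certain. It does not reconcile the two totals, because the Randomization and Blinding section assigns the number on enrolment and the Sample Size section attributes the loss to trial dropout.

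Three stronger readings are tempting, and the document supports none of them.
- That the trial is underpowered. Followed as written, the Sample Size section yields more completers than it requires.
- That rounding to a multiple of 4 is misapplied because 30 is not such a multiple and would leave a block half filled. No block size is stated, only that block sizes will be appropriate, and rounding 21 up to 24 does no harm.
- That the registry entry carries the same mistake. It is not at hand, so nothing can be said about it.

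**Conclusion.** The contradiction is real: the abstract's 24 randomised and the body's 30 randomised cannot both hold. The body should be taken as the plan, and the abstract appears to report the completer target as the number randomised. This is an inconsistency between abstract and body; the sample-size arithmetic is coherent.

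The consequence is conditional and modest. Recruiting to 30 gives an expected 24 completers and power of about 85%. Recruiting only to 24 would leave about 19 completers and power of about 75%, and it would miss the required 21 only if dropout exceeded 12.5%. These figures assume that 21 completers do give 80% power for 1.5 points, that the test is two-sided and uses within-participant differences, and that the 20% implied by 30 to 24 applies after randomisation.

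**What to change.** State one set of figures throughout: 30 participants randomised, 24 completers expected, and 21 completers needed for 80% power. Correct the abstract sentence to match. Saying in the Sample Size section that the 30 enrollees are the participants randomised, and giving the assumed dropout rate, would remove the remaining ambiguity.

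The cost is a wording change. The plan already provides for 30 enrollees, so no further participants are needed. Neither the block sizes nor the rounding to a multiple of 4 has to change.

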**Results:**

This trial was registered in the International Standard Randomized Controlled Trial registry March 15, 2016 (Number ISRCTN58259979), and it attained ethics approval on December 3, 2016 (Queen’s University Health Sciences & Affiliated Teaching Hospitals Research Ethics Board protocol number ANAE-287-15). The recruitment started in February 2017.

**Conclusions:**

This trial will provide evidence for the efficacy of ALA in fibromyalgia.

**Trial Registration:**

International Standard Randomized Controlled Trial Number (ISRCTN): 58259979; www.isrctn.com/ISRCTN58259979 (Archived by WebCite at http://www.webcitation.org/6og9JdiyZ)

## Introduction

Fibromyalgia is a multisystem disorder characterized by chronic widespread pain, sleep disturbance, fatigue, irritable bowel syndrome, depressed mood, and cognitive dysfunction, that is reflected in functional disability and impaired quality of life [1,2]. This condition is highly prevalent, with estimates suggesting that 1.6% of men and 4.9% of women are affected [3]; however, the reported prevalence of fibromyalgia is much higher in patients also diagnosed with migraine (22.2%) and low back pain (39%) [4]. Fibromyalgia not only causes suffering, but it is also a substantial financial burden. Canadian estimates put the annual direct health care costs of fibromyalgia at Can $350 million, and annual private insurance costs at Can $200 million [5]. The average 6-month direct and indirect costs of fibromyalgia per person in Canada are Can $2298 and Can $5035, respectively [6]. In the United States, for every dollar spent on fibromyalgia-specific claims, employers spend another US $57-US $143 on additional direct and indirect costs [7]. Thus, in addition to being devastating to the afflicted individual and his or her family, fibromyalgia also exerts a major adverse socioeconomic impact on the society.

Chronic widespread pain is the predominant feature of fibromyalgia [1]. Many drug (eg, nonsteroidal antiinflammatory drugs [NSAIDs], antidepressants, opioids, and anticonvulsants) and nondrug (eg, exercise, acupuncture, cognitive-behavioral therapy) treatments have been evaluated in hundreds of randomized controlled trials (RCTs) [8,9]. In addition to exercise and cognitive behavioral therapy, pharmacotherapy remains an important treatment for fibromyalgia [8]. Evidence-based treatment recommendations from the European League Against Rheumatism, the American Pain Society, and the Association of the Scientific Medical Societies in Germany have included amitriptyline, cyclobenzaprine, tramadol, gabapentin or pregabalin, fluoxetine, and duloxetine [10]. Unfortunately, the current therapies available for treating fibromyalgia do not provide complete relief from all the symptoms. In fibromyalgia (and most other chronic pain conditions), current drugs reduce pain by only 25-40% on average, and meaningful relief occurs in only 40-60% of the patients [9,11]. This is in part due to incomplete efficacy and dose-limiting adverse events associated with these drugs (eg, sedation, cognitive dysfunction, and dizziness). Moreover, some of these side effects (eg, fatigue and cognitive dysfunction) are also common symptoms of the disease, so current drug therapies can actually exacerbate fibromyalgia symptoms. There is some evidence to suggest that combinations of drugs with different mechanisms of action and nonoverlapping side effects may provide superior relief for fibromyalgia patients while minimizing adverse events [12]; however, there are currently very few high-quality trials testing this hypothesis and a related systematic review is currently underway [13].

Careful and extensive clinical observations have identified several similarities between neuropathic pain and fibromyalgia (eg, comorbid depression, disturbed sleep, and similar profiles of sensory symptoms and sensory dysfunction) indicating that considerable similarities and overlap exists between these two conditions, that suggests the possibility of common underlying mechanisms such as central sensitization to nociceptive stimuli [14]. Therefore, it is perhaps not surprising that several treatments effective in neuropathic pain (eg, tricyclic antidepressants, selective norepinephrine reuptake inhibitor [SNRI] antidepressants, gabapentin, and pregabalin) are also effective in fibromyalgia [10]. These converging lines of evidence provide a sound rationale for evaluating new therapies for fibromyalgia that are known to be efficacious in neuropathic pain. One such emerging intervention of interest is antioxidant therapy.

There is growing evidence implicating a role of reactive oxygen species and antioxidants in pain modulation [15-18]. In a mouse pain model, levels of the endogenous antioxidant superoxide dismutase were correlated with the degree of capsaicin-induced hyperalgesia, such that lower antioxidant levels were associated with greater hyperalgesia [19]. These findings suggest that injury-induced pain processing is due in part to accumulation of reactive oxygen species. Furthermore, early preclinical and clinical evidence suggests that various antioxidant compounds have analgesic effects in various pain conditions including vitamin C in complex regional pain syndrome [20], soy protein in neuropathic pain [21], and a combination of different antioxidants in pancreatitis [22]. Alpha-lipoic acid (ALA) has antioxidant activity in its reduced and oxidized forms [23], and is likely the antioxidant that has been studied most extensively for its analgesic efficacy in humans. Over the past several decades, ALA has been studied in the setting of pain in dozens of investigations. Preclinical evidence for analgesic mechanisms of ALA include decreased sensitivity to noxious stimulation through inhibition of T-type calcium (Cav3.2) channels [24]. Clinically, at least sixteen RCTs of ALA involving more than 1320 participants have reported reductions in pain and other diabetic neuropathy symptoms [25-28]. Although symptomatic improvement with ALA has been demonstrated mostly in diabetic neuropathy populations, evidence also suggests the potential for efficacy in other pain conditions such as chemotherapy-induced neuropathy [29,30] and burning mouth syndrome [31].

Current fibromyalgia treatments provide clinically relevant pain relief in only some patients and also frequently exacerbate other disabling features of fibromyalgia. An analgesic agent that does not cause central nervous system depression would be of great benefit to patients suffering from fibromyalgia. Unfortunately, there is no evidence to support the efficacy of acetaminophen or NSAIDs in fibromyalgia, and any potential benefits of NSAIDs are greatly outweighed by their gastrointestinal and other adverse effects such that NSAIDs are recommended against in recent fibromyalgia guidelines [10]. Thus, there is clearly a desperate need for new fibromyalgia treatments with greater analgesic efficacy, but also with a better safety and tolerability profile that is best suited to the constellation of fibromyalgia-related symptoms. ALA has demonstrated safety and efficacy (number-needed-to-treat=~6) in neuropathic pain in 16 RCTs of more than 1320 patients to date [27]. Given the similarities between neuropathic pain conditions and fibromyalgia, we hypothesize that ALA will be effective in reducing pain in fibromyalgia patients. Furthermore, given that ALA is nonsedating with no reported fatigue or cognitive dysfunction, we expect that ALA will have the added benefit of not exacerbating these fibromyalgia-related symptoms.

## Methods

### Ethics Approval

This study underwent ethics review and received a compliance notice from the Queen’s University Health Sciences & Affiliated Teaching Hospitals Research Ethics Board. This study protocol will be conducted in accordance with the principles of the Declaration of Helsinki and also consistent with the International Council for Harmonisation Good Clinical Practice: Consolidated guideline.

### Aims and Hypothesis

The objective of this trial was to evaluate the safety and efficacy of ALA in treating pain in participants with fibromyalgia. Our primary hypothesis is that ALA is safe and superior to placebo in treating pain in fibromyalgia.

### Design

This is a double-blind, randomized, 2-period crossover controlled trial comparing ALA to placebo in adults with fibromyalgia (Figure 1). Each of the 2 treatment periods will be 5 weeks in duration, and the entire trial will be 10 weeks long for each participant. Participants will be randomized to one of the two treatment sequences. The randomization sequence will be generated using the Web-based program—randomization.com (Dallal, Tufts University). Participants in sequence 1 will take active inert placebo capsules during the first 4 weeks of the trial (followed by a 1-week washout period) and will subsequently take active ALA capsules for the next 4 weeks of the trial (followed by a 1-week washout period). Participants in sequence 2 will take active ALA capsules during the first 4 weeks of the trial (followed by a 1-week washout period) and will subsequently take inert placebo capsules for the next 4 weeks of the trial (followed by a 1-week washout period). See Figure 1 for a trial design schematic.

**Figure 1 figure1:**
[figure not shown]
Flow of participants through the trial.

**Figure 2 figure2:**
[figure not shown]
Trial design schematic representation.

### Setting

Investigators work in a tertiary care health sciences center in Kingston, Ontario, Canada.

### Participants

Men and women aged 18 years and older meeting the 2016 American College of Rheumatology revised diagnostic criteria for fibromyalgia will be considered for recruitment following informed consent. The inclusion and exclusion criteria are given in Textboxes 1 and .

Inclusion criteria for the study.Adults aged 18 years and olderDiagnosed with fibromyalgia using the 2016 American College of Rheumatology revised diagnostic criteriaExperiencing daily moderate pain (≥4/10 on a Numerical Rating Scale) for at least three monthsWomen of childbearing potential must have a negative serum beta-human chorionic gonadotropin (HCG) test and are required to use a highly effective form of contraception while on trialHave the necessary abilities, visual acuity, and English language skills to complete questionnaires and pain diaries and to participate in telephone communication with study nurses to permit titration of the study drugs

Exclusion criteria for the study.Presence of a painful condition, including inflammatory rheumatic disease, more than 50% as severe as, but distinct from, fibromyalgiaWomen who are pregnant or lactatingWomen of childbearing potential not using adequate contraceptivesEnd-stage kidney or liver diseaseUnstable cardiovascular disease (myocardial infarction within the preceding year, unstable angina, or congestive heart failure) or clinically relevant abnormal 12-lead electrocardiogramAny poorly controlled medical condition that, in the opinion of the investigator, would interfere with proper conduct of the trialSevere depression, as determined by a Beck Depression Inventory-II score of 29 or more; suicidal ideation, as determined by a Beck Depression Inventory score of 2 or more; any current major psychiatric disorder (eg, schizophrenia, bipolar disorder, and so on) that is not well-controlledHypersensitivity to any of the study medicationsAny current alcohol or drug abuse or dependence (except nicotine and caffeine). Participants with a history of abuse/dependence with more than 1 year of abstinence may be considered for inclusionThose taking more than 90 mg morphine equivalents per day

### Randomization and Blinding

We will use a balanced Latin Square crossover design in which participants will be allocated to one of the two treatment sequences of ALA and placebo. At the beginning of the trial, an investigational pharmacist will use a computer-generated randomization process to prepare a concealed allocation schedule to randomly assign the treatment sequences, in appropriate block sizes, to a consecutive series of numbers. On enrollment, each participant will be assigned to the next consecutive number, and the corresponding series of study medications will be dispensed (eg, ALA followed by placebo or placebo followed by ALA). Study medications will be formulated in an identical fashion across treatment periods. Treatment codes for each study participant will be generated by an investigational pharmacist and will not be disclosed to study personnel or participants until completion of all participants in the trial. Study outcome measures will be evaluated and recorded by the research study nurse who will be blinded (as will the rest of the research team) to treatment group assignments until trial completion. As an assessment of blinding to treatment group, each participant and the study nurse will complete a blinding questionnaire at the end of each treatment period.

